#### Secondary outcomes

The secondary outcomes of this study include self-reported outcomes, objective outcomes of physical function, and a biological indicator outcome.

KOOS Pain [29]: A 9-item pain evaluation scale, with scores ranging from 0 to 100. Lower scores indicating greater levels of pain.

KOOS knee-related Quality of Life (QOL) [29]: A 4-item quality of life evaluation scale, with scores ranging from 0 to 100. Lower scores indicating poorer quality of life.

Short Form 6 Dimensions (SF-6D) [31]: A quality of life evaluation scale derived from the SF-36, with 6 items for estimating the cost-effectiveness. Higher scores indicating poorer quality of life.

Five-level EuroQol five-dimensional questionnaire (EQ-5D-5L) [32]: A generic preference-based quality of life evaluation scale, with 5 items for jointly estimating the cost-effectiveness. Higher score indicates poorer quality of life.

Credibility/Expectancy Questionnaire [33]: A 6-item scale for evaluating patients’ credibility/expectancy to the intervention. This scale will be measured within 5 min after the finish of first treatment.

Patient’s global assessment (PGA) [34]: A 5-point ordinal scale for evaluating the patient’s overall perception of the effect.

Thirty-second Chair Stand Test (30s-CST) [35]: A test of lower body strength, dynamic balance and sit-to-stand activity. The patient will be requested to sit in a chair with their feet flat on the floor, shoulder width apart, knees bent slightly more than 90 degrees, arms crossed at wrists and close to their chest. Then, within 30 seconds, the patient will be measured the times they could complete as many full stand-to-sit cycles as possible. The hips and knees require be fully extended when standing up; the hips require to fully touching the chair when sitting down. Additionally, the height of chairs needs to be unified.

Forty meters (4x10m) Fast Paced Walk Test (40m FPWT) [36]: A test of walking speed over short distances and changing direction during walking. Patients will be asked to walk back and forth twice on the 10-meter walkway completely as fast as possible without running. The time spent walking on the walkway will be recorded.

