Daily Physical Activity level (DPA): DPA contains 1 week’s daily average steps and walking time, which will be recorded by portable pedometers (Polygon H-215G; Bestek Electronics Co., Ltd, Taiwan, China). The patient will be provided with a pedometer at the commencement of the preparatory period. The pedometer is required to be worn at all times except sleeping, bathing and water sports. At each visit, the researcher will record the data collected by the pedometer for the preceding week.

Rescue medicine: Any use of rescue medicine will be recorded, including the time and dosage.

The Credibility/Expectancy Questionnaire will be measured within a 5-minute period following the initial treatment session. PGA will be measured at week 4, 8, 16 and 24. Rescue medicine will be recorded within 24 hours after each taking. Other secondary outcomes will be assessed at baseline and at week 4, 8, 16 and 24. Additionally, the NRS and the KOOS ADL will be assessed at week 4, 16 and 24 as secondary outcomes.

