### Sample size

Based on previous study [13,37], we estimated that the difference in effect size between the 2 groups would be no more than 0.5. Between-group variations in NRS and KOA were expected to be 1 and 8 at week 8, respectively, with the standard deviations (SD) of 2 and 16. With 2-side α = 0.025 (adjusted for two primary outcomes), 77 patients per treatment group are required to test a difference in effect size of 0.5 with 80% power. Taking into account a 20% dropout rate, a total of 196 patients are expected to be recruited.

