### Statistical analysis

SPSS 26.0 software will be used for statistical processing. Measurement data will be expressed as mean and standard deviation, or median and interquartile ranges. Counting data will be expressed as percentages.

All randomly grouped patients with at least 1 session of intervention received will be included in the modified intention-to-treat (mITT) analysis. Multiple imputation will be used to fill the missing data. Five datasets for the missing data will be imputed by the observation value of age, gender, body mass index, KL grade and outcomes from other timepoints. All between-group comparison on repeated measure continuous outcomes (NRS, KOOS ADL, KOOS QOL, SF-6D, EQ-5D-5L, 30s-CST and 40m FPWT, DPA, except PGA) will be assessed by mixed-effect models using outcome scores at all assessed timepoints as the dependent variable, intervention as the main factor, and the baseline value as the covariate. PGA will be assessed by chi-squared test. Sensitivity analysis will be conducted on the primary outcomes (NRS and KOOS ADL) in 2 datasets. First, the dataset without imputation will be analyzed to address potential imputation bias. Second, the per-protocol (PP) set, which will be defined as receiving a minimum of 19 (electroacupuncture) or 12 (exercise) sessions with no obvious protocol violation, will be analyzed to address the compliance. For primary outcomes, *P* < 0.025 will be considered statistically significant (Bonferroni correction). Secondary outcomes will be considered exploratory, and *P* < 0.05 will be considered statistically significant.

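### The five-grade ordinal patient's global assessment is compared with a chi-squared test that, on its ordinary reading, ignores the order of the grades: valid, but inefficient against a consistent shift

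*Protocol article*

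**What the plan says.** Under Secondary outcomes, the protocol article describes PGA as "A 5-point ordinal scale for evaluating" the patient's overall perception of the effect. On timing, "PGA will be measured at week 4, 8, 16 and 24"; there is no baseline value.

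Under Statistical analysis, the repeated continuous outcomes go into mixed-effect models, and PGA is expressly left out of that list ("30s-CST and 40m FPWT, DPA, except PGA"). For PGA the whole instruction is "PGA will be assessed by chi-squared test". The section gives no table layout, degrees of freedom, trend version, rank test, ordinal model or responder cut-off. It does say that count data will be presented as percentages.

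On status, "Secondary outcomes will be considered exploratory", with 0.05 as the significance level. The Sample size section covers only the two primary outcomes and states no power, effect or distribution for PGA.

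**The concern.** The article names a property of the scale in one section and names a test that does not use it in another. A Pearson chi-squared test on two arms by five grades asks whether the two sets of five proportions differ in any way. Relabelling or shuffling the grades leaves the statistic unchanged, so its 4 degrees of freedom are spread over every possible pattern of difference. The pattern that usually matters for a global rating is one arm sitting higher on the scale.

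Two things are at stake. First, a real shift in ratings is more likely to be missed than with a test that uses the order. Second, the p-value comes with no summary of which arm is rated better and by how much, whereas the mixed models planned for the continuous outcomes estimate a difference between arms. The trial's stated purpose is to describe how the two therapies differ, so an estimate is worth having for the patient's own verdict as well.

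**Working it through.** **Inputs from the protocol article.** Five ordered grades (Secondary outcomes). Chi-squared test, significance at 0.05 for secondary outcomes, taken as two-sided (Statistical analysis). 77 evaluable per arm, standardised effect 0.5, 80% power, two-sided alpha 0.025, 20% dropout, 196 in total (Sample size).

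**Assumptions, because the article gives no figures for PGA.** Pearson test on the full 2x5 table; several shapes of grade distribution; a consistent shift between arms, as a common odds ratio or as a shift on an underlying normal scale.

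**Step 1: the plan's own figure.** n per arm = 2(z₀.₉₈₇₅ + z₀.₈₀)² / 0.5² = 2(2.2414 + 0.8416)² / 0.25 = 76.04, rounded up to 77. This agrees with the article. Allowing for dropout, 77/0.8 = 96.25, so 97 per arm or 194 in total, close to the stated 196. So 77 per arm is a fair evaluable number.

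**Step 2: a check without simulation.** At the same noncentrality λ, compare 1 df with 4 df. For 80% power on 1 df at 0.05, λ = (1.960 + 0.842)² = 7.85. With 4 df the critical value is 9.49, and the power at λ = 7.85 is 59.5%. The loss is 20.5 points. The same loss is 19 points when the 1-df power is 50% (30.8% on 4 df) and 16 points when it is 90% (74.0% on 4 df).

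**Step 3: simulation of the two tests.** Pearson chi-squared (4 df) against the tie-corrected Wilcoxon rank-sum test, 77 per arm, 20,000 trials per setting. Five control distributions were used: 10/20/30/25/15%, uniform, bell-shaped (10/20/40/20/10%) and two skewed (5/10/25/40/20% and 2/8/20/40/30%). Ranges are over the five.

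| Assumed difference | Chi-squared, 4 df | Wilcoxon | Loss (points) |
|---|---|---|---|
| Odds ratio 1.25 | 7–8% | 12% | 4–5 |
| Odds ratio 1.5 | 15–17% | 28–30% | 12–13 |
| Odds ratio 2.0 | 42–45% | 65–67% | 22–23 |
| Odds ratio 2.5 | 69–72% | 88–89% | 17–19 |
| Odds ratio 3.0 | 86–87% | 96–97% | 10–11 |
| Latent shift 0.5 SD | 61–64% | 82–84% | 20–21 |

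With no dropout (98 per arm) and a 0.5 SD shift, power is 74–75% against 90–91%, a loss of about 16 points. With no true difference both tests reject in close to 5% of trials (about 4.3–5.4%). A linear-by-linear trend test performs almost exactly as the Wilcoxon test does.

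**Step 4: a pattern where the order does not help.** If one arm has grades 10/20/40/20/10% and the other is uniform, the arms differ in spread but not in location. Chi-squared then has about 74% power and Wilcoxon about 5%.

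The shape of the distribution hardly changes the loss. The size of the effect and the consistency of the shift do.

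**The case against.** **The 4-df form is inferred.** The article says only that a chi-squared test will be used. A trend chi-squared, or a 2x2 test on responders, would also fit those words, and under the trend version the loss disappears. This stands as a condition on the finding. It does not remove it: with an ordinal scale defined, five grades and no cut-off or trend named, the ordinary Pearson test is the natural reading. A named method is also not the same as detail left to a plan not shown.

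**A reader might infer a fixed loss of about 20 points.** The documents do not support that. They give no PGA effect or distribution. The 0.5 SD planning effect belongs to the primary outcomes, and the Sample size section presents it as a ceiling. The loss peaks near an odds ratio of 2.0 and is much smaller on either side.

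**A reader might infer that the test is wrong, or that direction would be unknown.** Neither follows. Type I error is held, and percentages by grade and arm are planned, from which direction can be read. What is lacking is a single estimate with an interval. A Wilcoxon p-value alone does not supply that either.

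**The gain depends on a roughly consistent shift.** With two quite different active treatments, a difference in spread cannot be excluded, and there the chi-squared test is the better detector. This stands as the one real cost of changing.

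**The consequence is small.** PGA is exploratory, and neither the sample size nor the co-primary conclusions depend on it. This stands in full.

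**Conclusion.** The point holds as a low-importance, inexpensive improvement. Read as the ordinary 2x5 Pearson test, the planned comparison discards the ordering that the article itself assigns to PGA. Against a consistent shift, with 77 evaluable per arm and two-sided alpha 0.05, the cost is roughly 4 to 23 points of power over odds ratios from 1.25 to 3.0, and about 20 points at a 0.5 SD latent shift. These figures rest on the Pearson reading, on proportional odds or a latent normal shift, and on assumed grade shares, though the shares matter little. This is lost efficiency and the lack of one directional estimate. It is not bias, and it does not affect the primary results.

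**What to change.** Replace the sentence on PGA with wording to this effect: at each visit, with week 8 foremost, PGA will be compared between arms by proportional-odds (ordinal logistic) regression with arm as the factor, reporting the common odds ratio with its 95% confidence interval; the percentage in each grade will be shown by arm. If a simpler test is preferred, name the Wilcoxon rank-sum test or the linear-by-linear trend test. If a trend chi-squared was meant all along, saying so is enough to recover the power.

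Keeping the grade percentages matters, because they would reveal a difference in spread that an order-using test sees less well. The cost is one line of analysis wording, with no new data, visits or patients, and ordinal regression is available in the stated software. The article reports that recruitment is under way, so the change should be dated and made before unblinded data are analysed.

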**Study design and methods:**

This is a randomized controlled trial in which 196 symptomatic KOA patients will be randomly assigned 1:1 either to the electroacupuncture group (n = 98) and the exercise group (n = 98). Patients in the electroacupuncture group will receive acupuncture with electric stimulation 3 times a week for 8 weeks, whereas patients in the exercise group will receive neuromuscular training twice a week for 8 weeks. Education concerning KOA management will be provided in both therapies. Co-primary outcomes include changes in numerical rating scale (NRS) and Knee injury and Osteoarthritis Outcome Score (KOOS) Activities of Daily Living (ADL) subscale from baseline at week 8. Secondary outcomes include KOOS Pain subscale, KOOS knee-related Quality of Life (QOL) subscale, Short Form 6 Dimensions (SF-6D), five-level EuroQol five-dimensional questionnaire (EQ-5D-5L), Credibility/ Expectancy Questionnaire, Patient’s global assessment (PGA), 30-second Chair Stand Test (30s-CST), 40m (4*10m) Fast Paced Walk Test (40m FPWT), and Daily Physical Activity level (DPA).

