### Outcomes

#### Primary outcomes

There are two primary outcomes in this trial. The primary outcome of pain will be changes in Numerical Rating Scale (NRS) and the primary outcome of function will be changes in the Knee injury and Osteoarthritis Outcome Score (KOOS) Activities of Daily Living (ADL) [29] from baseline at week 8. NRS is an 11-point pain assessment scale ranging from ‘no pain’ (0) to ‘worst pain’ (10). KOOS is an extension of the Western Ontario and McMaster University Osteoarthritis Index (WOMAC) [30], designed to evaluate knee injuries and osteoarthritis. KOOS Activities of Daily Living (ADL) subscale comprises 17 items and has a score range of 0–100, with lower scores indicating worse dysfunction.

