## Discussion

KOA has long plagued the elderly, and it’s also a significant contributor to societal burden. Patients tend to seek nonpharmacologic therapies, such as acupuncture (the most popular complementary medicine [38]) and exercise (a core component of guideline-based recommendations [6,7]). Numerous studies supported the respective benefits of acupuncture and exercise, yet tiny of them compared the differences to guide appropriate treatment for specific populations.

In this trial, frequencies of the two therapies will not be equal, which is to reflect the practical frequency in clinical practice. All intervention details were designed to closely emulate the clinical reality, with the aim of reacting real situation in clinical practice. Since the main symptoms of KOA are pain and dysfunction, both will be selected as primary outcomes separately in order to clearly elucidate the differences in symptom improvement between the two interventions. In addition to self-reported outcomes, objective functional tests will also be included, thus enabling the detection of both perceived effect and objective activity improvement. In terms of generalizability, the current 2 centers incorporating both traditional Chinese medicine hospital and modern hospital. Consequently, a broader spectrum of patients will be included. Further, the exploratory analyses will focus on providing evidence for different populations.

One limitation of the trial is that neither the therapist nor the patient can be blinded, leading to potential instability of the results. Patients’ expectations will enhance the placebo or nocebo effect, and the lack of blinding may bring bias. Nevertheless, this study was designed to compare the effectiveness rather than the efficacy, thus the nonspecific effect should not be excluded. Patient’s expectations will be assessed to help explaining the difference between the two therapies. In addition, the researchers maintained a neutral position to therapies, which can reduce the bias from the study design. Further limitation involves the sustainability of benefits. For a chronic disease like KOA, a 24-week assessment may not suffice to offer a comprehensive understanding. Definitive conclusions about the long-term effects between the 2 interventions necessitate further real-world studies with long term follow-up.

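### The two primary outcomes are tested by plain Bonferroni, which is valid; a Holm step-down would be a cheap improvement that keeps the 5% family-wise error and is never less powerful

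*Protocol article*

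**What the plan says.** The Primary outcomes section states: "There are two primary outcomes in this trial". They are the week 8 changes in NRS (pain) and KOOS ADL (function). The Discussion adds that "both will be selected as primary outcomes separately", so that differences in pain and in function can each be described. The abstract uses another label: "Co-primary outcomes include changes in numerical rating scale (NRS") and KOOS ADL.

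The decision rule is in the Statistical analysis section: for the primary outcomes, a P value below 0.025 "will be considered statistically significant (Bonferroni correction"). The Sample size section uses the same level: "With 2-side α = 0.025 (adjusted for two primary outcomes"), with 77 patients per group to "test a difference in effect size of 0.5 with 80% power". The article describes no step-down or other recycling of alpha.

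**The concern.** The trial wants a separate answer on pain and on function. Under the stated rule, each outcome must pass 0.025 whatever the other shows. Suppose NRS gave P = 0.001 and KOOS ADL gave P = 0.03. Function would be declared not significant, although a procedure with the same 5% family-wise bound would allow the claim. What is at stake is some power on whichever outcome has the larger P value. Control of type I error is not in question.

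**Working it through.** **Inputs.** From Sample size: "Between-group variations in NRS and KOA were expected to be 1 and 8 at week 8" (the second outcome is read as KOOS ADL), SDs 2 and 16, two-sided alpha 0.025 per outcome, 80% power, 20% dropout, 196 patients in total. Effect size: 1/2 = 8/16 = 0.5 for each outcome. The correlation r between the two test statistics is not given, so r = 0 to 0.9 is assumed.

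**The plan's own figure.** n per group = 2(z₀.₉₈₇₅ + z₀.₈₀)²/d² = 2(2.2414 + 0.8416)²/0.25 = 76.04, rounded up to 77. This matches. Power at 77: the expected z is 0.5 × √(77/2) = 3.102, and Φ(3.102 − 2.241) = 80.5%. A t-test calculation gives 78 per group; 78/0.8 = 97.5, so 98 per group and 196 in total. The plan is sized for Bonferroni and delivers its stated power per outcome.

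**Holm rule.** Test the smaller P at 0.025. If it is rejected, test the larger at 0.05.

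**Why the error bound holds under any correlation.**
- Both nulls true: an error needs the smaller P to pass 0.025. That has probability at most 0.025 + 0.025 = 0.05.
- One null true: an error needs that outcome's P to pass 0.05. That has probability at most 0.05.
- No null true: no false positive is possible.

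**Hand check at r = 0.** Power at the 0.05 level is Φ(3.102 − 1.960) = 87.3%, so an outcome falls between the two thresholds with probability 0.8734 − 0.8054 = 0.0680.
- Holm power per outcome: 0.8054 + 0.8054 × 0.0680 = 86.0%.
- Both outcomes: Bonferroni 0.8054² = 64.9%; Holm 0.6487 + 2 × 0.8054 × 0.0680 = 75.8%.
- At least one, either rule: 1 − 0.1946² = 96.2%.

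**Simulation.** Bivariate normal z-statistics, 4 million draws per setting, 77 per group, effect size 0.5 on both outcomes. Results in %:

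| r (assumed) | Per outcome: Bonferroni | Per outcome: Holm | Both: Bonferroni | Both: Holm | At least one (either rule) |
|---|---|---|---|---|---|
| 0 | 80.5 | 86.0 | 64.9 | 75.8 | 96.2 |
| 0.3 | 80.5 | 85.5 | 67.4 | 77.2 | 93.7 |
| 0.5 | 80.5 | 85.0 | 69.4 | 78.5 | 91.6 |
| 0.7 | 80.5 | 84.6 | 72.0 | 80.0 | 89.1 |
| 0.9 | 80.5 | 83.8 | 75.6 | 82.0 | 85.5 |

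The gain is 5.5 down to 3.3 points per outcome (86.0 − 80.5; 83.8 − 80.5) and 10.9 down to 6.4 points for both (75.8 − 64.9; 82.0 − 75.6).

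**Error rates.** With both nulls true, the family-wise error is the same under either rule: 4.96% (r = 0), 4.64% (r = 0.5) and 4.30% (r = 0.7). With one true null and an effect of 0.5 on the other outcome, the false-positive rate on the null outcome is 2.5% under Bonferroni. Under Holm it is 4.5%, 4.25% and 4.0% at those three correlations. In that setting, power for the real effect moves only from 80.5% to about 80.7%.

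**The case against.** The strongest reply is that nothing here is wrong. The threshold is prespecified with its reason, the sample size uses the same alpha, and the 80% power per outcome is delivered without Holm. Choosing between two valid procedures is partly preference. This stands, and it is why the point is an improvement and not an error.

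Three further points also stand:
- **Bonferroni does buy something.** A reader might infer that its stricter second threshold gives up power for nothing. That is true of the 5% family-wise bound. But when only one effect is real, Bonferroni holds the other claim to 2.5% false positives, against about 4-4.5% under Holm.
- **Intervals.** Holm's extra rejections are exactly the second outcomes with P from 0.025 up to 0.05. In each of these, the 97.5% interval includes zero. Under the present rule, tests and 97.5% intervals agree.
- **The gain is conditional.** Its size depends on an undocumented correlation and on both effects being real. The larger gain concerns winning on both outcomes, for which the article sets no power target.

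A reader might also infer from the abstract's label that both outcomes must be significant, which would contradict an alpha split. The documents do not support this. The Primary outcomes, Sample size, Statistical analysis and Discussion sections together make the rule clear: each outcome is its own claim. The label is a matter of wording only.

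None of this removes the advantage: at the family-wise level that the plan has chosen, Holm never rejects less than Bonferroni.

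**Conclusion.** The point holds as a cheap improvement. The current rule is valid, internally consistent and powered as stated; the documents do not support a reading that the trial is underpowered or that its error control fails. On the plan's own effect size of 0.5 for both outcomes, Holm adds about 3 to 5.5 points of power per outcome and about 6 to 11 points for both, and nothing for at least one. These figures assume 77 analysable patients per group, normal test statistics and a correlation between 0 and 0.9. The Sample size section describes 0.5 as an upper limit, so absolute power would be lower under either rule if the true effects are smaller.

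**What to change.** By a dated amendment made before unblinding, replace the primary decision rule with: order the two primary P values; test the smaller at 0.025; if it is significant, test the larger at 0.05 (Holm); otherwise declare neither significant.

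For reporting, state that the decision rests on the Holm-adjusted P value. Give the 97.5% interval together with the 95% interval, the latter labelled as unadjusted, so that a second outcome won at P from 0.025 up to 0.05 is not misread. In the same amendment, the abstract's label could be changed to two primary outcomes, either of which may be claimed.

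Cost: a short text change and an update of the registered plan. It needs no extra patients, visits or data, and the target of 196 stays valid. The article reports that recruitment was still open and that statistical analysts are blinded, so on that status the change can be made without knowledge of results. The amendment should acknowledge that protection of a single null outcome loosens from 2.5% to about 4-4.5%, still under 5%.
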